## Abstract

**Background:**

Delirium is a common occurrence in patients undergoing major cardiac surgery and is associated with a number of adverse consequences for the individual, their family and the health system. Current approaches to the prevention of delirium include identifying those at risk together with various non-pharmacological and pharmacological strategies, although the efficacy of these is often modest. Emerging evidence suggests that melatonin may be biologically implicated in the development of delirium and that melatonin supplementation may be beneficial in reducing the incidence of delirium in medical and surgical patients. We designed this trial to determine whether melatonin reduces the incidence of delirium following cardiac surgery compared with placebo.

**Methods/Design:**

The Healthy Heart-Mind trial is a randomized, double-blind, placebo-controlled clinical trial of 3 mg melatonin or matching placebo administered on seven consecutive days for the prevention of delirium following cardiac surgery. We will recruit 210 adult participants, aged 50 and older, undergoing elective or semi-elective cardiac surgery with the primary outcome of interest for this study being the difference in the incidence of delirium between the groups within 7 days of surgery. Secondary outcomes of interest include the difference between groups in the severity and duration of delirious episodes, hospital length of stay and referrals to mental health services during admission. In addition, we will assess differences in depressive and anxiety symptoms, as well as cognitive performance, at discharge and 3 months after surgery.

**Discussion:**

The results of this trial will clarify whether melatonin reduces the incidence of delirium following cardiac surgery.

**Trial registration:**

The trial is registered with the Australian Clinical Trials Registry, trial number ACTRN12615000819527 (10 August 2015).

**Electronic supplementary material:**

The online version of this article (doi:10.1186/s13063-016-1163-1) contains supplementary material, which is available to authorized users.

## Background

Delirium is a syndrome characterized by cognitive impairment and attention deficits that usually develop over a short period of time and fluctuate in intensity and presentation. Several behavioral and psychological symptoms can accompany delirium, such as agitation, psychosis, disturbed sleep and mood changes, all of which can cause distress to patients, their families and medical staff [1]. Delirium has a prevalence of 15 % among hospitalized older adults [2], although it goes unrecognized in 32–66 % of them [3]. Delirium is particularly common after surgery and is estimated to occur in up to 42 % of patients undergoing major cardiac procedures [4–7].

Delirium is associated with poor clinical outcomes, including higher risk of dementia and admission to residential care, as well as increased mortality [8]. Delirious patients experience more postoperative complications [4], higher readmission rates, poorer functional outcomes [9], and increased length of stay [10]. The annual cost of delirium to the health care system in the United States is estimated to fall between US$38 billion and US$152 billion [11]. Delirium may persist for several weeks in up to a third of patients, leading to further increased morbidity and mortality [12].

Postoperative cognitive decline following cardiac surgery is estimated to occur in 24 to 79 % of patients and persistence of symptoms is common [13]. Newman and colleagues followed 261 patients for 5 years after coronary artery bypass grafting (CABG) surgery [14]. They found that 53 % of participants exhibited cognitive decline at discharge, and although this proportion decreased at the 6-month follow-up (24 %), the prevalence rose again after 5 years to 42 %. These findings are consistent with the possibility that postoperative cognitive dysfunction (of which delirium is an important contributing factor) worsens long-term cognitive outcomes [15].

Various factors increase the risk of delirium, including age, pre-existing cognitive impairment, disruption of the circadian rhythm, dehydration, malnutrition, and certain medications [16]. Major cardiac surgery increases the risk of delirium, with critical contributing factors including the type of surgery, use of hemofiltration, medications administered, length of surgery, time on bypass, high transfusion requirement, postoperative hypertension, patient’s age and whether the surgery was elective [7]. Some of these risk factors are amenable to change, whilst others (e.g., age) are not.

Current approaches to the prevention of delirium in hospitalized patients consist of both non-pharmacological and pharmacological approaches, of which the former are arguably more effective [17]. Non-pharmacological approaches involve addressing multiple risk factors in a systematic manner together with education and environmental manipulation, although only relatively modest reductions in delirium incidence are usually attainable [18]. Pharmacological approaches may include treatment with antipsychotic drugs, cholinesterase inhibitors, hypnotics, anti-inflammatory drugs and gabapentin [19], but supportive evidence of efficacy is not compelling. In addition, all of these agents carry a relatively high risk of adverse effects.

### Evidence linking melatonin and delirium

Melatonin is a serotonin-derived hormone secreted by the pineal gland. It plays a pivotal role in the regulation of the sleep-wake cycle [20], and has numerous other biological and physiological functions. One of the typical features of delirium is the disruption of the sleep-wake cycle and circadian rhythm [1]. This raises the possibility that melatonin-related pathways may mediate the expression of delirium [21]. In addition, older people are more prone to sleep disorders arising from degeneration of suprachiasmatic nuclei and resulting lower melatonin levels [22]. Serum melatonin levels decrease post surgery [23] and after the administration of certain opioids [24], possibly contributing to the disrupted sleep-wake cycle and increased risk of delirium that these patients experience. Plasma melatonin levels have been shown to be lower in delirious patients following major surgery [25] and urine concentrations of melatonin metabolites are altered in people who are delirious [26]. It is also possible that melatonin demand is higher after surgery, thereby leading to a relative depletion and greater risk of delirium [27].

Melatonin secretion is stimulated by low exposure to light and peak production corresponds to the main sleep period in humans. Melatonin is metabolized in the liver and excreted by the kidneys and has a short half-life (40–50 minutes) [28]. The safety profile of melatonin in clinical trials is comparable to placebo [29].

### Existing preliminary data suggest that melatonin might prevent and treat delirium

Four clinical trials of melatonin or melatonin agonists for the prevention of delirium have been performed to date (summarized in Fig. 1), although none of these have been conducted in cardiac surgery patients. The earliest of these enrolled 300 patients undergoing hip arthroplasty under spinal anesthesia [30]. Participants were randomly allocated to one of four groups: control, melatonin 5 mg, clonidine and, lastly, a group given midazolam. The melatonin group received one dose in the evening prior to surgery and 90 minutes pre-operatively. The author reported a significant decrease in the prevalence of postoperative delirium in the melatonin group compared with placebo (9.4 % versus 32.7 %, *p* = 0.003; numbers needed to treat (NNT) = 5). Moreover, treatment with melatonin was associated with remission of delirium in 58.1 % of postoperative patients.

**Fig. 1 Fig1:**
[figure not shown]
Meta-analysis of available clinical trials. Forest plot showing the published clinical trials of melatonin for the prevention of delirium (primary outcome of incident delirium). The meta-analysis shows a slight benefit for melatonin over placebo although small sample size and study heterogeneity prevents firm conclusions from being drawn

In a trial of acutely ill medical in-patients aged 65 and older, Al-Aama and colleagues randomly allocated 72 patients to melatonin and 73 to placebo [31]. Patients consumed 0.5 mg of melatonin or placebo every night for 14 days, or until discharge. Delirium was diagnosed according to the Confusion Assessment Method (CAM) [32]. Melatonin use was associated with a lower risk of delirium (12 % versus 31 %, *p* = 0.014; NNT = 6), with an odds ratio (OR) adjusted for dementia and comorbidities of 0.19 (95 % CI 0.06 to 0.62). These differences remained significant when patients with prevalent delirium on admission were excluded (19.2 % in the placebo and 3.6 % in the melatonin group, *p* < 0.02).

More recently de Jonghe and colleagues completed a multicenter, placebo-controlled clinical trial in 378 patients undergoing hip surgery [33]. Participants received 3 mg of melatonin for 5 days starting within 24 hours of admission. The authors found no difference in the incidence of delirium between the melatonin (55/186, 29.6 %) and placebo (49/192, 25.5 %) groups (difference 4.1 %, 95 % CI −0.05 to 13.1), but reported that a smaller proportion of participants in the melatonin group experienced a long-lasting episode of delirium (>2 days) (25.5 % versus 46.9 %, *p* = 0.02). Lastly, Hatta and colleagues conducted a small trial of the melatonin agonist, ramelteon (8 mg per day for 7 days) in 67 acutely unwell medical patients [34]. They reported a significant decrease in the incidence of delirium in those taking ramelteon as compared to placebo (3 % versus 32 %, *p* = 0.003; NNT = 4). The forest plot presented in Fig. 1 summarizes the efficacy data of these trials.

The results of these trials suggest a potential role for melatonin in preventing and treating delirium in older adults, although conflicting results, methodological issues (e.g., absence of a placebo-control group) and differing patient populations prevent firm conclusions from being drawn and generalized.

### Rationale for the proposed study

Delirium is frequent after cardiac surgery and is associated with many adverse consequences. Emerging evidence suggests that melatonin may be biologically implicated in the development of delirium and that melatonin use may be beneficial in reducing the incidence of delirium in medical and surgical patients, but these results require replication in differing at-risk populations.

### Objectives

The primary outcome of interest for this study is the difference in the incidence of delirium (as determined by the CAM and *Diagnostic and Statistical Manual of Mental Disorders, version 5* (DSM-5) criteria) between the placebo and melatonin groups within 7 days following cardiac surgery. Secondary outcomes of interest include the difference between groups in the severity and duration of delirious episodes, hospital length of stay and referrals to mental health services during the admission. In addition, we will assess for differences in mood and anxiety symptoms and cognitive performance at discharge and at 3 months after surgery.

### Trial design

The Healthy Heart-Mind trial is a randomized, double-blind, placebo-controlled clinical trial of 3 mg melatonin or matching placebo administered on seven consecutive days for the prevention of delirium following cardiac surgery (two arms, 1:1 allocation, parallel design). This study follows SPIRIT guidelines, and the relevant checklist is available as an additional electronic file (Additional file 1). 

## Methods

### Participants and setting

We will recruit 210 participants undergoing elective or semi-elective cardiac surgery in Perth, Western Australia. All outpatients undergoing elective cardiac surgery attend the pre-assessment clinics before admission (usually a week prior). Potential participants will be approached during this clinical review and offered an opportunity to participate in the study. In addition, we will approach patients admitted to cardiology and general hospital wards awaiting surgery on a semi-elective basis; e.g., stable patients admitted with a myocardial infarction or unstable angina deemed suitable for surgical intervention.

### Eligibility criteria

Participants will be:Aged 50 years and olderUndergoing elective or semi-elective cardiac surgery (on or off cardiopulmonary bypass) for coronary artery bypass grafting (CABG) and/or valvular surgery

We will exclude participants who:Decline or are unable to give informed consentAre undergoing emergency surgeryAre not fluent in written or spoken English (for the purposes of being able to complete the study assessments and questionnaires)Have a contraindication to taking melatonin, such as a prior allergic reactionAre currently using melatoninHave a diagnosis of dementia or score ≤19 on the Telephone Interview for Cognitive Status-modified (TICS-m) [35]Have a score ≥15 on the Alcohol Use Disorders Identification Test (AUDIT) [36]

### Interventions

Eligible participants will be randomly allocated to treatment with 3 mg melatonin or matching placebo for seven consecutive nights, beginning 2 nights prior to the surgery. The contents of each capsule will be administered via a nasogastric tube for those who are unable to swallow.

### Outcomes

We will use a set of well-validated instruments and scales to assess for the presence of delirium and measure its severity, as well as to assess other outcomes of interest for this study.

#### Establishing the presence of delirium

The CAM will be used to establish the presence of delirium. The first assessment will take place in the pre-assessment clinic or hospital ward prior to the surgery (usually a week before but this can vary) and then daily, beginning 1 day post surgery and continuing for up to 7 days or until discharged (whichever comes first). The CAM was developed in 1988–1990 and is a widely used and well-validated screening tool for delirium, with sensitivity of 94 % (95 % CI 91–97 %) and specificity of 89 % (95 % CI 85–94 %) [37]. A trained research nurse will rate the scale on the basis of a standardized interview with the patient that includes a brief cognitive assessment. Case notes and nursing staff reports will be reviewed as part of the assessment. The diagnosis of delirium will be confirmed in consultation with an experienced psychogeriatrician ([name] or [name]). The CAM rates nine areas (acuity, attention, thought organization, level of consciousness, orientation, memory, perception, psychomotor tempo and sleep), but delirium is only diagnosed when there is evidence of acute onset, inattention, fluctuating mental state and either disorganized thinking or disturbed consciousness. The CAM has been successfully adapted for use in the intensive care setting [38]. The rating of the CAM takes about 10 minutes to complete.

#### Establishing the severity of delirium

The Memorial Delirium Assessment Scale (MDAS) [39] will be used to assess the severity of delirium and will be administered daily if delirium is present. The MDAS is a 4-point, 10-item (range 0–30) clinician-rated scale designed to quantify the severity of delirium in a medically ill patient population. It takes approximately 10 minutes to complete.

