### Sample size

The primary outcome of the proposed trial is the development of delirium within 7 days of surgery. We based our sample size on the trial of Al-Aama and colleagues [31]. They reported a 15.6 % absolute reduction (19.2 % versus 3.6 %, *p* < 0.02) in the incidence of delirium in their sample. Assuming a 15.6 % absolute risk reduction in our patients with a conservative 25 % incidence of delirium in the control group and an incidence of 9.4 % in the intervention group, we will require 91 participants per group (182 participants in total) to detect a difference of this magnitude with a power of 80 % and a two-sided alpha of 0.05. After allowing for a conservative loss to follow-up of 15 % [31], we calculated that we will need to recruit 210 participants (105 per group). A defined secondary outcome for this trial is cognitive performance 1 week and 3 months after surgery. A study with 100 participants per group at the 3-month follow-up will have 81 % power to declare as significant between group difference of 2 points in the change from baseline score of the TICS-m (1 versus 3 points, SD 5). A change of less than 2 points would be of uncertain clinical significance.

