### Statistical methods

We will analyze and store the data using reliable statistical software (Stata, StataCorp, College Station, TX, USA). Baseline data will be compared using descriptive statistics, Student *t* tests for normally distributed continuous variables, the Mann-Whitney test for ordinal variables and Pearson’s chi-square statistic for categorical variables. The primary outcome analysis will be intention-to-treat and will use multilevel logistic regression of panel data (xtlogit). This approach to the analysis of the data allows for the inclusion of all available information and for the investigation of interactions between terms (such as intervention and time). A similar approach will be used to analyze other binary outcomes (e.g., use of psychotropic medication). We will use multilevel mixed models to investigate changes in scores of the MDAS and TICS-m (continuous variables). All probability tests will be two-tailed and will be declared as significant when *p* < 0.05.

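### Post-surgery MDAS is scored only when delirium is present, so the planned severity comparison rests on a subset selected by the primary outcome and can be biased in either direction

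*Protocol article*

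**What the plan says.** The Objectives section lists as secondary outcomes "the difference between groups in the severity and duration of delirious episodes". The section on establishing the severity of delirium says that the MDAS "will be used to assess the severity of delirium and will be administered daily if delirium is present", on a scale from 0 to 30. Table 1 marks the MDAS at baseline without qualification and, at every later time point (daily, discharge or day 7, and 3 months), only if required.

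Statistical methods gives the analysis: "We will use multilevel mixed models to investigate changes in scores of the MDAS and TICS-m (continuous variables"). Intention-to-treat is stated for the primary outcome analysis. Nothing says what value a participant or a day without delirium takes in the severity comparison. No analysis is named for duration.

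The Confusion Assessment Method (CAM), by contrast, is done daily in all participants from the day after surgery to day 7 or discharge. The primary outcome, as Sample size puts it, is delirium developing within 7 days of surgery.

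**The concern.** The collection rule makes the existence of a post-surgery MDAS score depend on the primary outcome. A mixed model uses the scores that were recorded, so the arms are compared among participants who became delirious. If melatonin changes who becomes delirious, the delirious participants in the two arms are different kinds of patient and randomisation no longer makes them comparable.

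The usual defence of a mixed model, that missing scores are ignorable given the observed ones, does not apply. An absent MDAS on a CAM-negative day means no delirium; it is not an unobserved severity. Treating it as missing lets the scores of delirious participants stand in for those who had none.

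At stake is the reading of a named secondary outcome. A drug that prevents mild cases could appear to worsen severity, and one that prevents severe cases could appear to improve it, in both instances with no change in any remaining case. The same applies to duration if it is averaged over episodes, and the Discussion says the trial will determine an effect on duration.

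**Working it through.** **Inputs from the protocol (Sample size section).** "25 % incidence of delirium in the control group and an incidence of 9.4 % in the intervention group", power 80%, two-sided alpha 0.05, 91 per group, 105 per group recruited.

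**1. Reproduce the plan's own figure.** With mean rate (0.25 + 0.094)/2 = 0.172, the pooled-variance formula without continuity correction is

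n = [1.960·√(2·0.172·0.828) + 0.842·√(0.25·0.75 + 0.094·0.906)]² / 0.156² = 90.7, rounded up to 91 per group.

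This matches, so the rates can be used for what follows.

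**2. Participants with post-surgery MDAS scores.**

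| Per arm | Control | Melatonin |
|---|---|---|
| 91 | 91 × 0.25 = 22.8 | 91 × 0.094 = 8.6 |
| 105 | 105 × 0.25 = 26.3 | 105 × 0.094 = 9.9 |

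The smallest difference detectable with 80% power is (1.960 + 0.842)·√(1/23 + 1/9) = 1.10 SD, or (1.960 + 0.842)·√(1/26 + 1/10) = 1.04 SD.

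**3. Extreme case.** The share of control-arm cases assumed prevented is 0.156/0.25 = 62.4%. Assume severity is normal, exactly the mildest 62.4% are prevented, and the rest are untouched. The cut is at z = 0.316, and the mean of the remaining 37.6% is φ(0.316)/0.376 = 0.3795/0.376 = 1.01 SD above control. Nobody was made worse.

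**4. Less extreme cases.** These rest on assumptions that are not in the protocol: MDAS in control cases normal with mean 15 and SD 5, 105 per arm, a t test standing in for the mixed model, and r as the correlation between mildness and being prevented. Remaining cases are left unchanged. Differences are melatonin minus placebo.

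| r | Delirious only (points) | Chance of significant apparent harm | All randomised, non-delirious = 0 (points) |
|---|---|---|---|
| −0.5 | −2.5 | under 0.1% | −2.6 |
| 0 | 0.0 | 3% | −2.3 |
| 0.3 | +1.5 | 12% | −2.2 |
| 0.5 | +2.5 | 25% | −2.1 |
| 0.8 | +4.0 | 61% | −2.0 |

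At r = −0.5 the delirious-only test shows a significant apparent benefit in about 25% of trials, again with no remaining case changed. The all-randomised comparison favoured melatonin on average in every row and gave no significant harm in any simulated trial.

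**5. A different mechanism.** Suppose delirium occurs when a normal latent severity passes a threshold and melatonin shifts everyone down. The mean excess above the threshold is φ(t)/p − t. For p = 0.25, t = 0.674 and the excess is 0.60 SD; for p = 0.094, t = 1.317 and the excess is 0.47 SD. Delirious-only severity is then slightly lower on melatonin, by 0.13 SD, although the shift itself is 1.317 − 0.674 = 0.64 SD.

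**6. An example in the Background.** The hip-surgery trial is reported with delirium in 55/186 on melatonin and 49/192 on placebo, and with episodes over 2 days in 25.5% versus 46.9%, p = 0.02. Since 46.9% exceeds the placebo incidence of 25.5%, the denominator must be delirious patients. The inferred counts are 0.255 × 55 = 14 and 0.469 × 49 = 23. An uncorrected chi-square on 14/55 versus 23/49 gives p = 0.022, matching the stated value. Over all randomised patients the same counts are 14/186 (7.5%) versus 23/192 (12.0%), p = 0.15. The choice of denominator decides the conclusion; there the conditional version favoured melatonin.

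**The case against.** The strongest reply is that Statistical methods does not restrict the MDAS model to delirious participants, that Table 1 gives everyone a baseline score, and that the handling of delirium-free days is the kind of detail an analysis plan supplies. With baseline in the outcome vector, every participant would enter the model.

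Part of this stands. A reader might infer that never-delirious participants have no MDAS at all, or that change has no starting value. Table 1 does not support either inference. A reader might also see a contradiction between text and table; there is none of substance, because the text rule reads naturally as governing the daily assessments, where Table 1 says the same. The baseline score does not rescue the comparison, however. After surgery, never-delirious participants still contribute no score, and the model would treat their absence of delirium as ignorable missingness. The collection rule, the outcome wording and the model are all stated, and together they produce the problem. That goes beyond omitted detail.

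On duration the reply is stronger. No duration analysis is stated, and daily CAM in everyone allows delirium days to be counted for all. What remains is that the outcome as worded refers to episodes and so conditions on having one.

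It is also fair that the 1 SD figure needs perfect sorting by severity, which nothing in the protocol supports, and that the bias vanishes at r = 0.

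**Conclusion.** The point holds for post-surgery MDAS severity. As written, the comparison rests on about 23 versus 9, or 26 versus 10, participants selected after randomisation by the primary outcome. The bias ranges from none, through about +1.5 to +4.0 points at r from 0.3 to 0.8 (assumed SD 5), to about 1 SD in the extreme; it reverses if severe cases are preferentially prevented. The case counts depend only on the protocol's assumed rates. The sizes of the bias depend on assumed severity distributions.

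A reader might go further and infer that an effective drug would be expected to look harmful. The documents do not support that: they give no information on which cases melatonin would prevent, and a plain shift in latent severity gives slightly lower severity among melatonin cases. The direction is unknown.

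The duration wording shares the conditioning, but no wrong duration analysis has been fixed. The consequence is confined to secondary outcomes; the primary incidence comparison is not touched by this point. It should be corrected, and the article states that recruitment had not begun.

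**What to change.** Define both secondary outcomes in all randomised participants:

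- **Duration:** number of delirium days from day 1 to day 7, with 0 for those never delirious.
- **Severity:** peak MDAS, with never-delirious participants in the lowest rank.
- **Analysis:** a rank or ordinal method, such as a Wilcoxon test or a proportional-odds model, with a prespecified rule for death and for discharge before day 7. Several choices are defensible; what matters is that one is fixed in advance.
- **Reporting:** label comparisons of MDAS and duration among delirious participants only as descriptive.

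The cost is a change of wording. The CAM is already done daily in everyone and the MDAS on delirious days, so no assessment is added. The downside is that the severity effect is expressed as a rank or ordinal effect rather than a mean MDAS difference.
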